### Main analysis—sequential design with the CSW approach based on age at enrollment

2.5

Emulated target trials assign men into one of the two screening arms based on their screening pattern during the eligibility period, which starts when they attain the age of interest for the study (75–79 yr) for the first time and every month thereafter (eg, at age 75 yr, 75.083 yr, 75.167 yr, and so on).

Screening is ascertained within the 1st month from trial initiation, representing the eligibility and assignment period. Eligible men with at least one PSA test in this period will be assigned to the screening arm. Those with no PSA test in this window will be assigned to the control arm. Assignment ascertainment is assumed to be accurate for all participants, as the STHLM0 contains the data on PSA testing for men living in Stockholm and who were tested in Stockholm since 2007 [22]. Considering the assumptions of causal inference frameworks [19], the following three principles are assumed to be fulfilled:1.Positivity: Every man living in Stockholm within the age group of interest has a nonzero chance of deviating from the protocol at any point during the assessment period, and every eligible man is assumed to have had the opportunity to undergo a PSA test.2.Consistency: The survival outcome we observe for the men under the given screening strategy is the same as the outcome that would have occurred if we had explicitly assigned these patients to follow the same strategy (ie, their potential outcome). As such, the screening protocol is assumed to have been defined clearly and applied consistently throughout the study period in our study. Moreover, we assume that the statistical models used in the analysis (described below) are specified correctly.3.Exchangeability: There are no unmeasured confounders; all factors that influence both the screening assignment and the likelihood of deviating from the protocol have been measured. We assume based on the confounders accounted for in the study (described below) that we address the potential factors that impact the screening assignment.

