#### Data preparation and choice of confounders

2.10.1

Data on all men living in Stockholm will be used, and ascertainment of time zero will be performed for all eligible men with no information on the variables necessary for the analysis missing. As men can continuously be eligible to be included in the sequential trials, the choice of time zero will follow the recommendation of Hernán et al [17], and emulation will be done repetitively during the eligibility period between 2007 and 2023. The confounders of interest are age (continuous), trial year (categorical; from 2007 to 2023), country/region of birth (categorical; Sweden, Nordic, European Union, and others), income (categorical; five quintiles), previous hospitalization during the past year (yes/no), number of hospitalizations during the past year (continuous), number of outpatient specialized health care visits (continuous), non–age-adjusted Charlson Comorbidity Index (continuous, based on adaptations for register-based Swedish data [20], and cumulatively computed, based on the past 5 yr until the end of the previous calendar year before the assessment), education (categorical; ≤9 yr of formal education, 10–12 yr of formal education, and ≥12 yr of formal education), civil status (categorical; not married, married, divorced, and widowed), current cancer diagnosis excluding PCa (yes/no), and family history of PCa (yes/no, based on father, brother[s], or son[s] diagnosed with PCa).

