#### Survival analysis

2.10.4

The analysis will be conducted using Stata 18 (Stata Corporation, College Station, TX, USA). Flexible parametric survival models will be used to model the log cumulative hazard with natural splines. Selection of the number of degrees of freedom for the baseline hazard will be done by evaluating the Akaike's Information Criteria [23]. Time-dependent coefficients will be used to account for a potential time-varying effect of the screening. Since men can participate in several trials, the variance-covariance matrix will be estimated using the clustered sandwich estimator. The stabilized inverse probability of screening weighting (IPW) will be generated using logistic regression. In presence of extreme weights, IPW will be truncated at the 99th percentile [21] and then multiplied by the IPCW. The product will be used to weigh the likelihood of the flexible parametric models. The user-written command stpm3 will be used to fit the flexible parametric survival models [24].

Standardized model-based cumulative incidence functions (CIFs) will be plotted and reported for all outcomes, and the difference in CIFs will also be plotted and reported at 5, 10, and 15 yr of follow-up. Standardization will be done over the empirical distribution of the confounders using the command standsurv [25]. The CIF difference for both the PCa-specific mortality and the all-cause mortality will be reported.

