### Potential strengths and limitations

3.3

Our study will leverage the STHLM0, which has near complete information on all PSA tests in Stockholm, with linkage to national Swedish registers allowing the capture of diverse lists of potential confounders [22]. In our planned study, we consider the emulation of pragmatic target trials suitable for addressing the research questions at hand. Moreover, the potential follow-up of up to 17 yr can provide sufficient time for the relevant outcomes to occur. Henceforth, this work has the potential to guide decisions on PCa screening cessation, addressing an important need among men who undergo opportunistic testing despite the lack of guidelines for this age group.

Despite these considerations, the study has potential limitations. First, our analysis plan assumes adherence to the assigned arm at each trial, which might not be ideal. Some of the men who will be considered as screened might have been prompted to undergo a PSA test following the symptoms of metastasis or urinary retention. However, the cause of the PSA test cannot be discerned from the register data. The diagnosis if preceded by symptoms is captured in the register but has incomplete information [39]. Additionally, men who underwent a PSA test within the study period due to health checkup following previously elevated tests are classified as screened in the study. However, due to the shift to organized PCa testing [40], this approach might better reflect future screening directions of continuing screening in this age group that was initiated at an earlier age, instead of initiating screening in this age group. Second, unmeasured and residual confounding cannot be ruled out, and data on functionality, holistic objective health status, and disability are not available from the registers. Although we attempt to conduct a subgroup analysis based on the level of multimorbidity excluding those who are sickest, it would not granularly capture individual causes of the PSA testing. Additionally, men who are institutionalized might not have admission or usage of specialized outpatient care, underestimating their multimorbidity.

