The actual capture of the outcome in PCa-specific mortality might be challenging to ascertain without autopsy among older men as the quality of the cause-of-death reporting decreases with age, and the death certificate might be suboptimal to capture PCa mortality among the oldest age group [[41], [42], [43]]. This observation has been reported in Nordic countries [42,44]. Thus, the sticky-diagnosis bias might affect determining whether PCa was the cause of death among the screened men compared with the nonscreened men [45]. As such, evaluation of both all-cause and PCa-specific mortality would be warranted, and this misclassification could affect PCa mortality, but not all-cause mortality [46]. A comparison of the risks among younger age groups can assist in ascertaining whether a potential difference in direction is due to the limitations of death certificates in older age and the sticky-diagnosis bias.

Although the study focuses primarily on mortality outcomes, diagnosis outcomes are addressed only descriptively, and the quality-of-life outcomes are not available in the registries. These findings would be needed for a fully informed decision-making process and subsequent updates to clinical guidelines.

Positivity is assumed as part of the emulation of target-trial design [47]. However, this might not be feasible in real life, as men who are very frail would be evaluated differently by health care providers and might not be considered for screening by the urologist as they might not be able to tolerate even conservative therapy.

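### Outpatient visits are coded as one continuous confounder with no zero-visit term, although low recorded use may mix fit and frail men; part of the confounding may stay in the weights

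*Protocol article*

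**What the plan says.** Section 2.10.1 gives a coding for every confounder. Income is in quintiles, and trial year and education are categorical. Hospitalization enters twice, as "previous hospitalization during the past year (yes/no") and as "number of hospitalizations during the past year (continuous"). Outpatient care enters once, as "number of outpatient specialized health care visits (continuous"). The Charlson index and age are also continuous.

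Section 2.10.2 puts this list into the Cox model for the censoring weights. Section 2.10.4 adds that "The stabilized inverse probability of screening weighting (IPW) will be generated using logistic regression" and names no other covariate list. Natural splines are mentioned there only for the log cumulative hazard.

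On model form, section 2.5 states that "we assume that the statistical models used in the analysis (described below) are specified correctly". The descriptive table in section 2.10.3 covers screened men, and no comparison of weighted arms is described.

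Section 3.3 warns that "men who are institutionalized might not have admission or usage of specialized outpatient care, underestimating their multimorbidity", and that "men who are very frail would be evaluated differently by health care providers" and may not be considered for screening.

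**The concern.** Taken together, the two remarks in section 3.3 mean that little recorded care is not a reliable sign of good health. Men with no specialist visits may be fit, or they may be institutionalized, rarely tested and at high risk of death. If frequent attenders are also tested less and die more, testing is lower and mortality higher at both ends of the visit scale. One slope cannot follow such a curve. Weights built on it balance the mean number of visits but not its extremes.

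The plan already gives hospitalization a separate level at zero. It does not do so for outpatient visits, although the warning in section 3.3 names both. Any frailty imbalance left at low use would usually make screened men look healthier, the same direction as the benefit the study is looking for.

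**Working it through.** **Scale.** Section 2.12 assumes 35 000 deaths and 20% screened. With the Schoenfeld formula and two-sided alpha 0.05 (assumed, not stated), power = Φ(√(D·p·(1−p))·|ln HR| − 1.96). For the 1.5-point row (HR 0.956): √(35 000 × 0.2 × 0.8) = 74.83; 74.83 × 0.0450 = 3.37; Φ(3.37 − 1.96) = 92.0%, as in Table 1. So 1.5 points is the yardstick. It refers to 17 years and 80% mortality, while the calculation below uses 50% mortality, so compare orders of magnitude only.

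**Assumed inputs** (the documents give none of these except the 20%): visits negative binomial with mean 3 and dispersion 1, so 25% have zero; 20% tested; 50% mortality; no true effect. With x = ln(1 + visits):

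- logit P(test) = a + b(x − c)², b = ln(0.68)/1.4² = −0.197
- ln cumulative hazard = k + g(x − c)², g = ln(1.34)/1.4² = 0.149

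With c = 1.4, testing odds at zero visits are 0.68 of the peak and the hazard is 1.34 times its lowest value. The curvature is held fixed and the turning point c is moved. Differences are computed exactly over the visit distribution, with stabilized weights from a logistic model; the spline has three df.

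| c (visits) | Crude | Linear term | Linear + zero indicator | Spline + zero indicator |
|---|---|---|---|---|
| 0.4 (0.5) | −1.61 | −0.03 | +0.05 | 0.00 |
| 0.7 (1.0) | −0.84 | −0.15 | 0.00 | 0.00 |
| 1.0 (1.7) | −0.46 | −0.29 | −0.03 | 0.00 |
| 1.4 (3.1) | −0.62 | −0.60 | −0.07 | 0.00 |
| 1.8 (5.0) | −1.52 | −1.13 | −0.15 | 0.00 |
| 2.2 (8.0) | −3.14 | −1.90 | −0.29 | −0.01 |

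Values are percentage points, screened minus unscreened; negative favours screening. The share removed by the linear term runs from 98% (1 − 0.03/1.61) to about 3% (1 − 0.60/0.62).

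**Sensitivity.**
- Dispersion 2 with 2% tested: the linear residual is +0.05 at c = 0.4 and −2.73 at c = 2.2.
- At c = 1.4, dispersion 1 and 2% tested: a weaker pattern (odds 0.82, hazard ratio 1.22) leaves −0.21; a stronger one (0.56, 1.48) leaves −1.15. The stronger pattern at c = 2.2 leaves −3.91.
- With no turning point (c = 0), the linear term over-corrects by +0.12 to +0.85 over dispersions 0.7 to 2 and 2% or 20% tested.

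**Institutionalization as a hidden variable.** A separate simulation of 1 000 000 men added an institutionalized group, 80% of them with zero recorded visits, tested less (log-odds −2.0) and dying more (log-odds +1.5). Share of the crude bias removed as that group grows from 0% to 10%:

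| Visit pattern | Linear | Flexible |
|---|---|---|
| Monotone | 100% to 50% | 100% to 54% |
| Mild non-monotone | 72% to 29% | 100% to 52% |
| Strong V-shape | 32% to 16% | 100% to 60% |

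At 10% institutionalized, flexible terms still leave 40% to 48%. Only adding the institutionalization indicator itself brings the bias to about zero.

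**The case against.** The best reply is that the listed codings name variable types. Nowhere does the article say linear, and a condensed article may leave functional form and balance tables to a fuller plan. That stands as far as it goes: linear entry is the natural reading of the list, not a stated fact. But the article does fix codings confounder by confounder, and it gives hospitalization a zero level that it withholds from visits.

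Second, the shape is conjecture. Section 3.3 does not say that testing falls at high visit counts, and it gives no shape for the Charlson index or age. This stands too: the argument is strongest for visits, weaker for the Charlson index and the hospitalization count, and weakest for age.

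Third, a turning point near the mean of 3 visits is almost the least favourable for the share a linear term removes. The table confirms this; that row alone would mislead.

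Fourth, mixing within the zero-visit group is an unmeasured-variable problem that flexible terms cannot solve. Correct, as the second simulation shows. The article concedes residual confounding, plans an array-method analysis (section 2.11.2) and a Charlson-restricted subgroup (section 2.10.5). It also standardizes over the confounders (section 2.10.4), a second adjustment that these calculations omit. The array analysis, however, addresses unmeasured confounding, not misfit of a measured covariate.

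**Conclusion.** The point holds as a specification weakness that is cheap to remove, not as a demonstrated bias. As listed, visits have one continuous term, no zero level and no stated balance check, although section 3.3 gives a reason to distrust low values. At the middle curvature, the residual after weighting with a linear term is about 0 to roughly −2 to −3 points, mostly favouring screening, against a 1.5-point target. Steeper curves can exceed that range. All of this rests on assumed patterns.

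A reader might infer that frailty confounding is hardly removed. The documents do not support that: they give no data on the shape, and a linear term removes from almost none to nearly all of the assumed bias depending on where the curve turns. Nor does it follow that flexible terms would settle the matter, because institutionalized and fit men with zero visits would still be treated as alike.

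**What to change.** In section 2.10.1, state for the logistic and Cox weight models that:

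- outpatient visits enter with a zero-visit indicator plus a natural spline, or as categories with zero separate;
- the number of hospitalizations enters as a spline, keeping the planned yes/no term;
- the Charlson index enters as a spline.

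Add that weighted standardized differences between arms will be examined by category of each variable, including zero use, before outcomes are analysed. Fix in advance the threshold (for example 0.1) above which the weight model is respecified.

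Also state that this does not remove confounding by institutionalization within the zero-use group, which remains an unmeasured-confounding limitation to be covered by the planned array analysis.

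The cost is plan wording and about 10 to 15 extra parameters in more than 200 000 men, with slightly more variable weights.

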#### Statistical considerations

2.10.2

Regarding the CCW trial emulation, two arms will be constructed representing the two screening strategies compared in each pair (screening vs no screening). As the period of eligibility is long (age 75–79 yr), it would artificially inflate the benefit of the no screening strategy as it would contribute to more deaths before the time of censoring in the screening arm. Hence, the trials will be conducted every month during the eligibility period (ie, 75–79 yr of age). Those screened in the control arm will be censored at the first date of their screening during the eligibility 1-mo period, while those not screened in the intervention arm will be censored at the end of the eligibility 1-mo period. Since the datasets will be censored artificially, the inverse probability of censoring weighting (IPCW) will be constructed by applying Cox regression using the list of confounders outlined earlier. Considering that the dataset in the STHLM0 is large (>200 000 men in the age group since 2007) [22], it is computationally prohibitive to construct the censoring weights at each censoring event. We will therefore construct these at the end of the eligibility period. All the datasets will then be appended to perform the analysis and will account for the variance from the same individuals contributing multiple times to the analysis.

Any deviation from the analysis plan or the proposed study design will be described and justified in the study publication.

#### Descriptive statistics

2.10.3

To address the first research question on the characteristics of men who screen for PCa using PSA despite no clinical recommendations, the baseline clinical and demographic characteristics of men who are screened in this age group will be quantified in a descriptive table. Moreover, the outcomes of the screening if resulted in the diagnosis of PCa would be quantified in terms of Gleason group; tumor, node, and metastasis stage; status if preceded by symptoms; and clinical significance (defined for pragmatic reasons as Gleason group ≥3 + 4). Categorical variables will be reported in terms of numbers and percentages, while continuous variables will be reported in term of means and standard deviations, or medians and interquartile ranges if the standard deviation is large.

#### Survival analysis

2.10.4

The analysis will be conducted using Stata 18 (Stata Corporation, College Station, TX, USA). Flexible parametric survival models will be used to model the log cumulative hazard with natural splines. Selection of the number of degrees of freedom for the baseline hazard will be done by evaluating the Akaike's Information Criteria [23]. Time-dependent coefficients will be used to account for a potential time-varying effect of the screening. Since men can participate in several trials, the variance-covariance matrix will be estimated using the clustered sandwich estimator. The stabilized inverse probability of screening weighting (IPW) will be generated using logistic regression. In presence of extreme weights, IPW will be truncated at the 99th percentile [21] and then multiplied by the IPCW. The product will be used to weigh the likelihood of the flexible parametric models. The user-written command stpm3 will be used to fit the flexible parametric survival models [24].

Standardized model-based cumulative incidence functions (CIFs) will be plotted and reported for all outcomes, and the difference in CIFs will also be plotted and reported at 5, 10, and 15 yr of follow-up. Standardization will be done over the empirical distribution of the confounders using the command standsurv [25]. The CIF difference for both the PCa-specific mortality and the all-cause mortality will be reported.

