**Fig. 1 f0005:**
[figure not shown]
Flowchart showing inclusion into and exclusion from emulated target trials. (A) The main analysis inclusion based on age. (B) The sensitivity analysis based on calendar year. Cloning refers to the duplication of each participant in the study, which is later assigned to one of the two screening strategies. PSA = prostate-specific antigen.

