### Screening strategy

2.4

Two types of target-trial emulations are proposed, with both aimed to address the second research question but using different causal inference methods. Two different methods are performed to evaluate whether the results would agree, giving confidence to the conclusions made based on the findings of the study. The first method employs a sequential design and the clone-censor-weight (CCW) approach with enrollment/inclusion based on the attained age (main analysis). The second method performs the analysis based on the calendar year (sensitivity analysis). The CCW approach handles time-varying eligibility and treatment assignment while avoiding the immortal time bias, and the sequential design enables repeated trial emulation at multiple entry points to maximize generalizability and emulate real-world decision-making [20,21].

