#### Analysis based on calendar year

2.11.1

Emulated target trials with observational analog of an intention-to-screen analysis will be conducted, using the CCW method and sequential design every month in alignment to the main analysis. However, the month’s assessment will start from January 1, 2007. Men are ascertained for their screening within the month if they are eligible (75–79 yr). The intervention arm includes eligible men screened with PSA for PCa, while the control arm includes eligible men not screened for PCa during that specific month period. Follow-up starts on January 1, 2007 and ends on December 31, 2023, or when mortality occurs, whichever comes first.

Figure 1B illustrates the flowchart of the inclusion into the trial based on the sensitivity analysis.

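### The cloned analysis multiplies two weights for the same one-month screening decision; the second is redundant at best and can overcorrect, even reverse, the confounding

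*Protocol article*

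**What the plan says.** Two descriptions of how men enter the arms stand side by side in the protocol article.

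- **Cloning.** The Figure 1 caption states: "Cloning refers to the duplication of each participant in the study, which is later assigned to one of the two screening strategies". Statistical considerations (2.10.2) adds that "two arms will be constructed representing the two screening strategies compared in each pair (screening vs no screening"), and that "Those screened in the control arm will be censored at the first date of their screening during the eligibility 1-mo period". Unscreened clones in the screening arm are censored when the month ends. For this artificial censoring, "the inverse probability of censoring weighting (IPCW) will be constructed by applying Cox regression using the list of confounders outlined earlier". These weights are computed once, at the end of the window.
- **Assignment by observed test.** Section 2.5 says: "Eligible men with at least one PSA test in this period will be assigned to the screening arm". Men without a test go to the control arm.

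Survival analysis (2.10.4) then generates a stabilized inverse probability of screening weight by logistic regression. If weights are extreme, that "IPW will be truncated at the 99th percentile [21] and then multiplied by the IPCW", and the product weights the likelihood of the flexible parametric models. Results are standardized over the confounders. Section 2.9 sets an intention-to-screen contrast.

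**The concern.** Cloning makes the two arms identical in their confounders at time zero. The only selection the design introduces is the artificial censoring in the first month, and the IPCW exists to undo it. Under the intention-to-screen contrast no artificial censoring follows, so no second process is left for another weight to handle.

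A stabilized screening weight is the right tool for the other design, in which men are assigned by their observed test and not cloned. Using both corrects one decision twice. At stake is the weighted contrast for both mortality outcomes: the screening arm can be tilted towards the men least likely to be tested, who may also be those most likely to die.

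**Working it through.** **Algebra.** Let A be PSA status in the month, L the confounders and f(L) their distribution.

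1. A screening-arm clone stays uncensored when the man was screened, and a control-arm clone when he was not. The target IPCW in arm a is therefore 1/P(A=a|L).
2. The weighted confounder distribution in that arm is f(L)·P(A=a|L)·1/P(A=a|L) = f(L). One weight suffices.
3. The stabilized screening weight fitted on observed status is P(A=a)/P(A=a|L).
4. The product is P(A=a)/P(A=a|L)², and the arm's distribution becomes proportional to f(L)/P(A=a|L). Men unlikely to be in the arm are now over-represented.
5. If the logistic model is instead fitted on clone arm, P(arm|L) = 0.5 for everyone, the stabilized weight is 1, and the product equals the IPCW.

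**Size.** The protocol gives no figure for this and no monthly testing probability (the 20% in Power calculation is not described as monthly), so every input here is an assumption. Screening has no true effect and 25% of men are frail. Arm risk = Σ f·P·w·m / Σ f·P·w, where m is mortality.

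| Setting | Unweighted | IPCW only | Product | Product, screening weight capped at pooled 99th percentile |
|---|---|---|---|---|
| Monthly testing 2% fit, 1% frail; mortality 45%, 80% | −3.8 pp | 0.0 | +5.3 pp | +1.0 pp |
| Monthly testing 2% fit, 1.5% frail; mortality 45%, 70% | −1.3 pp | 0.0 | +1.5 pp | +0.3 pp |

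First row in full: P(A) = 0.75×0.02 + 0.25×0.01 = 0.0175.

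- Under the product, the screening arm is weighted in proportion to f/P: 0.75/0.02 = 37.5 fit and 0.25/0.01 = 25 frail. The frail share is 25/62.5 = 40%, against 25% in the population. Risk is 0.60×0.45 + 0.40×0.80 = 0.590.
- The control arm's frail share is 24.8% and its risk 0.537. The difference is +0.053.

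Why the cap bites: the screening weights of screened frail men are 0.0175/0.01 = 1.75 and 0.01875/0.015 = 1.25. These men are 0.25% and 0.375% of records, so a pooled 99th percentile reduces both weights to about 1.00. The cap does not always help. With half the men frail, testing at 25% and 15%, and mortality 70% and 90%, the product gives +3.1 pp with or without it.

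**Outcome-model adjustment.** In a simulation of 2,000,000 men (half frail, testing 25% and 15%, no effect), the product-weighted marginal difference was +0.032. After correct adjustment and standardization it was 0.001, the same as with the IPCW alone. Precision was lost: the effective size of the screening arm fell from 375,051 to 315,849, a loss of 1 − 315,849/375,051 = 16%. With a normal confounder shifting testing by 0.4 log-odds per SD, the effective fraction fell from 86% to 54%.

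**Cox tie handling.** Screening-arm censoring is tied at month end. With true probabilities of remaining uncensored of 0.03 (fit) and 0.01 (frail), a Cox fit with Breslow ties gave about 0.022 and 0.020. The IPCW then hardly varies with L, and the product is close to the screening weight alone. Efron ties gave 0.025 and 0.016, a partial double correction.

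**The case against.** A reader might infer that the plan is bound to reverse the confounding, or that the error equals the 1.5% absolute reduction for which Power calculation claims over 90% power. The document supports neither.

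- It does not say whether the logistic model is fitted on observed status or clone arm, or which covariates enter it. On clone arm, the extra factor is 1.
- Truncation can shrink the overcorrection, as the +1.0 and +0.3 pp results show. It is conditional on extreme weights, however, and the records over which the percentile is taken are not stated.
- Standardizing over the confounders implies that they are in the outcome model, and a correct outcome model removes nearly all of the bias.
- The Cox fit may not recover the screening probability, so the double correction may be only partial.
- This is a condensed article, and covariate lists for weight models commonly sit in a fuller plan.

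All of this stands as a limit on the size and certainty of the bias. None of it makes the extra weight useful. The multiplication is stated text, not an omission. The name of the weight and the assignment rule in 2.5 make observed screening the natural reading. Leaning on the outcome model gives up the protection that weighting is meant to add.

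One neighbouring issue is separate and is not evidence for this one. Section 2.4 says "Two different methods are performed to evaluate whether the results would agree", whereas the second analysis is again run "using the CCW method and sequential design every month in alignment to the main analysis". The same weighting would presumably carry over to it, so agreement between the two would not expose this problem.

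**Conclusion.** The rule is wrong as written: in the cloned analysis the IPCW already handles the one-month screening decision, and a second weight for it is either inert or an overcorrection. If the second weight models observed testing with the same confounders and the IPCW recovers the screening probability, the weighted contrast before outcome adjustment is off by about +1.5 to +5.3 pp in the two low-testing illustrations. With the pooled 99th-percentile cap it is off by about +0.3 to +1.0 pp. The direction is against screening when the men least often tested have the higher mortality. These sizes rest on assumed testing rates, frailty share and mortality under a true null. With a correct adjusted outcome model, what remains is dependence on that model and lost precision. Reversal is possible but not established.

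**What to change.** State one weight per design.

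1. In 2.10.4, delete the screening weight from the cloned analysis, weight the likelihood by the IPCW alone, and apply the planned 99th-percentile truncation rule to that weight. State the records over which the percentile is taken.
2. Because the IPCW then carries the whole correction, check that it restores the confounder distribution in each arm, given the tied censoring at month end.
3. Reconcile 2.5 (assignment by observed test, where the screening weight alone would apply) with the Figure 1 caption and 2.10.2 (cloning).
4. Optionally, run a non-cloned sequential analysis with the screening weight only as a second method.

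Items 1 to 3 cost wording changes, a small amount of recoding and a balance check. No new data are needed.
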